### Sample size calculation

According to a previous study, placebo is associated with high rates of resolution in a functional bowel disorder. Assuming that a difference of at least 30% between acupuncture and placebo is needed for a clinically important outcome, 51 patients per treatment group were deemed sufficient to achieve 80% power in detecting a treatment difference, based on a two-sided *χ*^2^ test without continuity correction at a significance level of 0.025 (used to maintain the overall significance level at 5%). Further assuming a 15% dropout rate, we concluded that we needed to recruit a total of 120 patients (60 per arm) for this trial to ensure statistically significant results. The calculation was performed using the StudySize 3.0 software (V. Frolunda, Sweden).

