### Outcomes

The primary outcome is the difference between baseline and 8 weeks and 14 weeks after randomization on IBS Symptom Severity Scale (IBS-SSS).

The secondary outcomes include (1) the difference between baseline and 8 weeks and 14 weeks after randomization on Hamilton Depression Rating Scale (HAMD-17), (2) the difference between baseline and 8 weeks and 14 weeks after randomization on Clinical Global Impression-Severity (CGI-S) and Self-Rating Depression Scale (SDS), and (3) the difference between baseline and 8 weeks and 14 weeks after randomization on IBS Quality of Life (IBS-QoL). IBS-SSS has been validated as a classical monitor of the disease since 1997 and has been widely adopted across IBS researches [30]. The specific assessment schedule is in Fig. 2. Safety profiles will be assessed by determining the important adverse events reported on in every treatment and follow-up interviews.

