### Statistical analysis

All efficacy and safety analyses will be conducted according to the intention-to-treat (ITT) principle. Missing values will be imputed by the last-observation-carried forward method. The statistical analysis will be performed using the Statistical Packages of Social Sciences (SPSS) for Windows version 25.0. The statistical significance is defined as a two-sided *P*-value of < 0.05. Baseline differences between the groups will be assessed with the use of Student’s *t*-test for normally distributed continuous variables and the non-parametric Mann-Whitney *U* test for non-normally distributed. For categorical variables, the chi-squared test or Fisher’s exact test will be used. Changes in IBS-SSS, HAMD-17, SDS, and IBS-QoL at each evaluation time point from baseline will be analyzed using the ANCOVA model, followed by the Bonferroni *t*-test to detect the differences between the two groups at each time point. Incidence of adverse events will be examined using the chi-square test.

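### The stated 80% power is for a chi-square comparison of two rates, not for the ANCOVA of IBS-SSS change that is the primary efficacy analysis

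*Protocol article*

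**What the plan says.** Three sections of the protocol article bear on this.

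- **Sample size calculation.** The starting point is that "placebo is associated with high rates of resolution in a functional bowel disorder". The effect is "a difference of at least 30% between acupuncture and placebo is needed for a clinically important outcome". The number follows as "51 patients per treatment group were deemed sufficient to achieve 80% power in detecting a treatment difference", with a two-sided chi-square "test without continuity correction at a significance level of 0.025". A 15% dropout allowance takes this to 60 per arm, 120 in total. The section ends by presenting that total as securing a significant result.
- **Outcomes.** "The primary outcome is the difference between baseline and 8 weeks and 14 weeks after randomization on IBS Symptom Severity Scale (IBS-SSS"). The inclusion criteria describe the scale as running from 0 to 500. All secondary efficacy outcomes are likewise differences from baseline on rating scales.
- **Statistical analysis.** "Changes in IBS-SSS, HAMD-17, SDS, and IBS-QoL at each evaluation time point from baseline will be analyzed using the ANCOVA model", followed by Bonferroni t-tests at each time point. Chi-square is named for categorical variables, directly after the baseline comparisons, and for adverse event incidence.

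**The concern.** The sample size section describes a test of two rates. The primary outcome is a continuous score and its test is ANCOVA. Nothing in the document turns the 30% into IBS-SSS points, defines an IBS-SSS cut-off that would count as resolution, or gives an SD or baseline correlation for the score.

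Power belongs to a particular test of a particular effect. A reader who takes 80% as the power of the primary analysis is therefore relying on a figure calculated for something else, and cannot tell what IBS-SSS difference the trial is able to detect. All three sections are in the article and fix their content, so this is a mismatch between stated elements and not a detail left to an analysis plan.

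**Working it through.** **1. Reproducing the plan's figure**

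Inputs from the Sample size calculation section: two-sided alpha 0.025, power 80%, difference 0.30 (read as percentage points, because the test is a chi-square), no continuity correction, dropout 15%. The control rate is not given, so it is varied.

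Formula per arm, with p̄ the mean of the two rates:

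n = [z(0.9875)·√(2p̄(1−p̄)) + z(0.80)·√(p₁(1−p₁) + p₂(1−p₂))]² / 0.30², where z(0.9875) = 2.2414 and z(0.80) = 0.8416.

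For 0.30 against 0.60: [2.2414 × 0.7036 + 0.8416 × 0.6708]² / 0.09 = 50.96, so 51.

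| Assumed control rate | Acupuncture rate | n per arm |
|---|---|---|
| 0.20 | 0.50 | 47 |
| 0.30 | 0.60 | 51 |
| 0.35 | 0.65 | 52 |
| 0.40 | 0.70 | 51 |
| 0.50 | 0.80 | 47 |

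The result is exactly 51 for control rates of about 0.27–0.30 and 0.40–0.43, and never above 52. The missing control rate therefore hardly affects the number. At alpha 0.05, or one-sided, the formula without continuity correction never exceeds 43. This confirms that 51 is a two-proportion figure at two-sided 0.025. For dropout, 51 / 0.85 = 60 per arm, 120 in total. The arithmetic is correct.

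**2. What the same numbers give for a continuous score**

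The detectable standardised difference with 80% power is approximately d = (2.2414 + 0.8416)·√(2/n). This is 0.611 for n = 51 and 0.563 for n = 60. The noncentral t distribution gives 0.618 and 0.569, which are used below.

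Baseline adjustment multiplies d by √(1 − r²), where r is the correlation between baseline and follow-up scores and d is in units of the follow-up SD. The document gives no r, so the values are assumptions.

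| Analysed per arm | Unadjusted | r = 0.3 | r = 0.5 | r = 0.7 |
|---|---|---|---|---|
| 51 | 0.618 | 0.590 | 0.535 | 0.442 |
| 60 | 0.569 | 0.543 | 0.493 | 0.406 |

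Both rows matter. 51 is the number left after the assumed dropout, but the Statistical analysis section specifies intention to treat with last observation carried forward, which can keep up to 60 per arm in the analysis.

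In points, assuming an SD of 80 to 100 and r = 0.5: 0.535 × 80 = 42.8 to 0.535 × 100 = 53.5 with 51 per arm, and 0.493 × 80 = 39.4 to 0.493 × 100 = 49.3 with 60 per arm.

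**3. Can power for the primary analysis be stated?**

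No. It depends on a true IBS-SSS difference and SD that the document does not give. As an illustration by noncentral t, unadjusted, with 51 per arm at alpha 0.025, power is about 60% for a true difference of 0.5 SD and 89% for 0.7 SD. Neither effect size comes from the document.

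**The case against.** The strongest reply is that a continuous analysis is usually more efficient than a dichotomised one, so a sample size from a binary calculation is conservative. Suppose that resolution is a cut of a roughly normal score. A 30-percentage-point difference then corresponds to Φ⁻¹(p + 0.30) − Φ⁻¹(p) SD, whose smallest value over all control rates is 0.77 (at p = 0.35, against 0.78 at 0.30 or 0.40). With 51 per arm at alpha 0.025, power for 0.77 SD is about 94%, before any gain from baseline adjustment.

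This stands as far as it goes, and it blocks two inferences that a reader might draw. One is that the trial is underpowered. The other is that a null IBS-SSS result could not speak to the effect used for sizing. The document supports neither. Low power figures can be produced only by choosing a smaller effect that the document does not state.

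The reply does not rescue the stated 80%, however. The link between resolution and an IBS-SSS cut-off is itself an assumption, and on that assumption the power would not be 80% either.

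A second reply is that chi-square tests are planned. They are, but for categorical variables and adverse events, with no categorical efficacy outcome for the 30% to refer to. The point is therefore limited to efficacy.

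**Conclusion.** The point holds in limited form. The calculation of 51 and 60 per arm is right for a two-sided chi-square comparison of rates 30 percentage points apart at alpha 0.025. The primary analysis is an ANCOVA of IBS-SSS change, so the 80% is not its power. The true figure may be higher or lower, and the document does not contain what is needed to say which.

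What can be stated is the detectable difference at alpha 0.025: about 0.62 SD (51 per arm) or 0.57 SD (60 per arm) unadjusted, and about 0.54 or 0.49 SD if r = 0.5 is assumed. These figures rest on approximate normality, equal SDs and 0.025 applying at each of the two primary time points. They do not allow for any dilution of the effect by carried-forward values.

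No bias and no inflation of type I error follow from this. It should be fixed because the power claim for the primary endpoint is unsupported as written.

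**What to change.** Keep 120 patients and rewrite the sample size paragraph:

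- Say openly that the number came from a binary calculation, and leave that basis visible. Replacing it silently would present 120 as the product of a calculation that was not done.
- Add the IBS-SSS difference, in points and in SD, that baseline-adjusted ANCOVA detects with 80% power, for 51 and for 60 analysed per arm.
- State the alpha used at each of the two primary time points. The sample size uses 0.025, while the Statistical analysis section gives 0.05 alongside a Bonferroni step.
- Show a range of SD and baseline correlation. The completed 20-patient pilot described under Trial status can inform these, but only imprecisely: with 10 per arm, a pooled SD on 18 degrees of freedom has a 95% interval of roughly 0.76 to 1.48 times its estimate.
- Remove the closing claim that this size secures a significant result, which no power calculation can do.

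The cost is one paragraph and no extra patients. The downside is that the resulting figure may look less favourable than the present 80%. Defining a responder outcome that matches the 30% and making it primary would also remove the mismatch, but it changes the primary endpoint and is the larger step.

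### The trial is sized at 0.025 per test to hold 5% overall, but the analysis section sets P<0.05 and leaves open whether its Bonferroni step covers the two primary visits

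*Protocol article*

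**What the plan says.** Three sections of the protocol article bear on this point.

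- **Outcomes.** The primary outcome is "the difference between baseline and 8 weeks and 14 weeks after randomization on IBS Symptom Severity Scale". That is one scale at two time points. The section does not say whether a benefit is needed at one visit or at both.
- **Sample size calculation.** The planned test is a two-sided chi-squared test without continuity correction, run "at a significance level of 0.025 (used to maintain the overall significance level at 5" per cent. The result is that "51 patients per treatment group were deemed sufficient to achieve 80% power in detecting a treatment difference". The section does not name the tests that share the 5%.
- **Statistical analysis.** "The statistical significance is defined as a two-sided *P*-value of < 0.05". The figure 0.025 does not reappear, and the primary outcome is not exempted. Changes from baseline in IBS-SSS, HAMD-17, SDS and IBS-QoL are analysed by ANCOVA, "followed by the Bonferroni *t*-test to detect the differences between the two groups at each time point". The set of comparisons that Bonferroni covers is not defined, nor whether 0.05 applies to raw or adjusted P-values.

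**The concern.** The sizing section recognises a multiplicity problem and pays for it with a stricter per-test level. The analysis section, which governs the trial's conclusion, does not clearly carry that level forward. The Bonferroni step is described as a comparison of two groups within a time point. Two groups give a single comparison at each visit, so the multiplier is 1 and the P-value is unchanged.

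What is at stake is the decision rule for the primary outcome. Suppose the IBS-SSS comparison gives a raw P of 0.04 at week 8 and a clearly null result at week 14. Under an unadjusted 0.05 threshold the trial could be called positive. Under 0.025 per visit (adjusted P = 2 × 0.04 = 0.08) it is negative. The present wording lets that choice be made after the data are seen.

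**Working it through.** **1. Was 0.025 really used for the sizing?**

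Inputs from Sample size calculation: difference 30% (read as 30 percentage points), two-sided alpha 0.025, power 80%, equal arms, no continuity correction, 15% dropout. The control rate is not given, so it is an assumption and was scanned from 5% to 70%.

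Formula per arm, with p̄ the mean of the two rates:

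n = [z(1−α/2)·√(2p̄(1−p̄)) + z(0.80)·√(p₁(1−p₁) + p₂(1−p₂))]² / (p₂−p₁)²

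With assumed rates of 0.30 and 0.60:

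n = [2.2414·√0.495 + 0.8416·√0.45]² / 0.09 = [1.5770 + 0.5646]² / 0.09 = 50.96, so 51 per arm.

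| Assumed control rate | n per arm, alpha 0.025 | n per arm, alpha 0.05 |
|---|---|---|
| 25% | 50 | 41 |
| 30% | 51 | 42 |
| 35% | 52 | 43 |
| 40% | 51 | 42 |
| 45% | 50 | 41 |

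At alpha 0.05 the requirement never exceeds 43 per arm anywhere in the scan. The stated 51 therefore does rest on 0.025. Dropout: 51 / (1 − 0.15) = 60 per arm, 120 in total. The plan's figures reproduce.

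**2. What are the two tests behind 0.025?**

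0.05 / 2 = 0.025, and the primary outcome has exactly two time points. That is the natural reading, but it is an inference.

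**3. Overall type I error if a win at either visit counts**

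For independent tests: 1 − (1 − 0.05)² = 0.0975 at 0.05 each, and 1 − (1 − 0.025)² = 0.0494 at 0.025 each.

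For correlated tests: 1 − P(|Z₁| ≤ c, |Z₂| ≤ c) under a bivariate normal distribution, with c the two-sided critical value. The documents give no correlation between the week 8 and week 14 tests, so a range is shown.

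| Assumed correlation | Each visit at raw 0.05 | Each visit at 0.025 |
|---|---|---|
| 0 | 9.75% | 4.94% |
| 0.5 | 9.07% | 4.65% |
| 0.7 | 8.35% | 4.30% |
| 0.9 | 7.04% | 3.62% |

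**4. If both visits must succeed**

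Testing each at 0.05 then keeps the error at or below 5% and no split is needed. The split to 0.025 makes sense only if either visit can carry the trial, so the sizing section points to an either-visit rule without stating it.

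**5. The sections under each reading**

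| Reading of the Bonferroni step | Level per primary visit | Agrees with the sizing section? |
|---|---|---|
| Between the two groups, within each visit (literal) | 0.05 | No |
| Across weeks 8 and 14 | 0.025 | Yes |

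**The case against.** The strongest reply is that the correction is already in the plan. A Bonferroni step over the two primary time points gives 0.05 / 2 = 0.025, exactly the figure used for sizing, and Bonferroni-adjusted P-values are properly compared with 0.05. On that reading the sections agree, the overall error is at most 5%, and the literal reading would make the prescribed step pointless. This stands as a plausible account of what the sponsor meant. It does not remove the point, because the sentence places the comparison between groups at each visit and the reader has to supply the family.

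A second reply is that families and success rules are often left to a statistical analysis plan. That is fair for an omission. Here, however, the article itself fixes two thresholds, 0.025 and 0.05, and does not connect them.

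Two stronger readings are tempting, and the documents support neither:

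- **That the type I error is nearly doubled.** This needs three things together: no adjustment across visits, a win at either visit, and nearly independent tests. The first is one of two readings and the second is not stated. The third is implausible for the same scale in the same patients. Last-observation-carried-forward would also copy week 8 values to week 14 for those who drop out in between, which raises the correlation further.
- **That the level is 0.05 / 3 = 0.0167, counting the week 5 visit, so that power is lost.** Outcomes limits the primary outcome to weeks 8 and 14. Any power figure would also need response rates that the plan does not give.

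**Conclusion.** The point holds as an unreconciled decision rule for the primary outcome, not as a proven loss of error control. Followed literally, and with success at either visit, the plan gives an overall type I error of about 7% to 10% where its own sizing section promises 5%. The upper end applies only to independent tests; assumed correlations of 0.5 to 0.9 give 9.1% to 7.0%. If the Bonferroni step spans weeks 8 and 14, or if both visits must succeed, the error is at most 5%. The text does not settle which applies.

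This should be corrected before any outcome data are compared by arm, because it decides what counts as a positive trial. The sizing arithmetic is sound on this point: 51 per arm reproduces at 0.025 for assumed control rates of 30% or 40%, and within one patient for rates of 25% to 45%.

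**What to change.** In Statistical analysis, state that:

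1. IBS-SSS change at week 8 and at week 14 forms the primary family of two comparisons;
2. success at either visit counts;
3. each visit is tested at two-sided 0.025 (equivalently, the P-value is Bonferroni-adjusted over the two visits and compared with 0.05), and each difference is reported with a 97.5% confidence interval so that intervals and decisions agree;
4. the unadjusted P<0.05 threshold applies to secondary outcomes only.

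In Sample size calculation, add that 0.025 refers to these two visits.

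The cost is a few sentences and a primary threshold stricter than 0.05. The sample size does not change on this account, because 51 per arm, and hence 60 after dropout, already assumes 0.025.

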### Statistical analysis

All efficacy and safety analyses will be conducted according to the intention-to-treat (ITT) principle. Missing values will be imputed by the last-observation-carried forward method. The statistical analysis will be performed using the Statistical Packages of Social Sciences (SPSS) for Windows version 25.0. The statistical significance is defined as a two-sided *P*-value of < 0.05. Baseline differences between the groups will be assessed with the use of Student’s *t*-test for normally distributed continuous variables and the non-parametric Mann-Whitney *U* test for non-normally distributed. For categorical variables, the chi-squared test or Fisher’s exact test will be used. Changes in IBS-SSS, HAMD-17, SDS, and IBS-QoL at each evaluation time point from baseline will be analyzed using the ANCOVA model, followed by the Bonferroni *t*-test to detect the differences between the two groups at each time point. Incidence of adverse events will be examined using the chi-square test.

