#### Withdraw from the trial

Participants will be allowed or asked to drop out from the trial if they:
Are lost to follow-upBecome pregnantDevelop serious adverse event (SAE)

Participants can withdraw from this clinical trial at any time. The date and reason for withdrawal should be stated. If possible, all subjects withdrawing from the study should continue to be followed up regularly on a measurement schedule with a final assessment. Participants who discontinue early will not be replaced.

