### Intervention

Each patient will be scheduled for a total of 12 treatment sessions, 30 min for each session, two times a week over a 6-week period. The selection of acupuncture points is based on the traditional Chinese medicine (TCM) theory [24–26] and evidence-based clinical research [22]. According to the traditional Chinese medicine (TCM) theory, the spleen transforms the food digested by the stomach into essences. It helps to transport throughout the body, while the liver ensures the smooth flow of Qi, modifies the activity of internal organs (Zang Fu), and is highly related to the emoto-psychological stage. Therefore, most TCM experts agree that the weakness of the spleen and stomach is the basic pathogenesis of IBS, while the stagnant among the liver and spleen can also cause a serious symptom of IBS [27]. Therefore, the principles of treatment of IBS are regulating the Qi movement among the liver and spleen. Thus, the following acupuncture points are selected for the treatment (Tables 1 and 2).

**Table 1 Tab1:** Checklist for items in STRICTA 2010

Item	Detail
**1. Acupuncture rationale**	**1a) Style of acupuncture** Manual and electro-acupuncture base on traditional Chinese medicine theory and evidences from previous clinical trials.
	**1b) Reasoning for treatment provided, based on historical context, literature sources, and/or consensus methods, with references where appropriate** According to systematic reviews and clinical experiences of our principal investigator and co-investigators.
	**1c) Extent to which treatment was varied** Standard treatment is used. No variation of treatment among patients.
**2. Details of needling**	**2a) Number of needle insertions per subject per session (mean and range where relevant)** 15 needles.
	**2b) Names (or location if no standard name) of points used (uni/bilateral)** Bilateral—Tianshu (ST25), Zusanli (ST36), Sanyinjiao (SP6), Toulinqi (GB15), Taichong (LR3), and Zhangmen (LR13). Unilateral—Baihui (GV20), Guanyuan (CV4), and Zhongwan (CV12).
	**2c) Depth of insertion, based on a specified unit of measurement, or on a particular tissue level** 10–30 mm.
	**2d) Response sought (e.g.,*****de qi*****or muscle twitch response)** De qi.
	**2e) Needle stimulation (e.g., manual, electrical)** Manual. Electrical—dense-disperse waves with 50 Hz at 10 volts.
	**2f) Needle retention time** 30 min.

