### Assignment and blinding

Simple, complete, non-sequential randomization numbers will be generated by the Random Allocation Software (Version 1.0.0), Isfahan, Iran, and kept by the principal investigator (PI). After the patient’s eligibility is confirmed, patients will be randomized to AC arm or SAC arm for 6 weeks. Only the acupuncturists are allowed to know the patients’ treatment. All other research members will be blind to the assignment. In addition, patients will also be blinded. They cannot visually detect sham or active acupuncture procedures.

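### Safety is analysed by intention to treat with no treated-patient set, and the Outcomes and Statistical analysis sections disagree on which adverse events count, so incidence may be understated

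*Protocol article*

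**What the plan says.** Three statements in the protocol article bear on the point.

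- **Population.** The Statistical analysis section opens with "All efficacy and safety analyses will be conducted according to the intention-to-treat (ITT) principle". The article names no separate set of treated patients for safety.
- **Outcome.** The Outcomes section says: "Safety profiles will be assessed by determining the important adverse events reported on in every treatment and follow-up interviews". The article does not say what makes an event important.
- **Test.** The Statistical analysis section says: "Incidence of adverse events will be examined using the chi-square test". Here the events carry no qualifier.

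Two further statements matter for how far the point goes. Directly after the population sentence comes a general rule: "Missing values will be imputed by the last-observation-carried forward method". It neither names nor excepts adverse events. And the section on withdrawal asks that, if possible, "all subjects withdrawing from the study should continue to be followed up regularly on a measurement schedule with a final assessment".

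Safety is a stated aim. The STRICTA checklist (item 6a) gives efficacy and safety against sham as the reason for the comparator, and the Discussion and conclusion says the trial will supply a basis for the safety of electro-acupuncture.

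**The concern.** Intention to treat protects an efficacy comparison from selective exclusion. It does not serve safety in the same way. A patient who was randomised but never needled cannot have a needling-related event, yet adds one to the denominator. A patient given the other arm's procedure has any event counted against the wrong one. The first effect can only lower incidence; the second has no fixed direction. The population sentence is an express rule and not a gap in a condensed article, so an analysis plan that added a treated-patient set would contradict it.

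The mismatch over *important* is separate. If the Outcomes wording governs, minor events such as bruising or local pain might never reach the table. If the analysis wording governs, they should. A reader of the final report could not tell which count was planned.

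At stake is the safety statement the trial intends to make about a procedure with 15 insertions per session over 12 sessions.

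**Working it through.** **Inputs from the article (Sample size calculation).** 51 evaluable patients per arm, 15% dropout, 60 randomised per arm. The article gives neither an adverse event rate nor a number of patients randomised but never needled; both are assumptions below.

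**The plan's own figure.** 51 / (1 − 0.15) = 60 per arm, which agrees. The 51 also reproduces: a two-sided chi-square test without continuity correction at 0.025 with 80% power needs 51 per arm for 30% v 60% or for 40% v 70%. The only use of these figures here is to bound the number untreated: 60 × 0.15 = 9 expected dropouts per arm.

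**Denominator effect.** Let *r* be the true incidence among treated patients and *u* the number per arm never needled. Then

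incidence shown = *r* × (60 − *u*) / 60

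| *u* per arm | factor | *r* = 10% | *r* = 20% | *r* = 30% |
|---|---|---|---|---|
| 0 | 1.000 | 10.0% | 20.0% | 30.0% |
| 1 | 0.983 | 9.8% | 19.7% | 29.5% |
| 3 | 0.950 | 9.5% | 19.0% | 28.5% |
| 9 | 0.850 | 8.5% | 17.0% | 25.5% |

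The last row requires every expected dropout to leave before the first session, so it is an extreme bound.

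**Difference between arms.** If *u* is equal in both arms, the risk difference shrinks by the factor in the table and the risk ratio is unchanged. If *u* differs, a difference can appear from nothing: with a true 20% in both arms, *u* = 3 in one and 0 in the other gives 19% v 20%.

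**Last observation carried forward.** For an ever/never count, a patient with a recorded event remains a case and a patient without one remains a non-case, whether or not a value is carried forward. What lowers the count after dropout is the missing observation itself. Suppose all nine dropouts are treated, leave halfway and have no later events recorded, with constant hazard and *r* = 20%: (51 × 0.20 + 9 × (1 − 0.80^0.5)) / 60 = (10.20 + 0.95) / 60 = 18.6%. All 60 were treated, so a treated-patient set shows the same 18.6%.

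**The *important* restriction.** The amount depends on the share of events judged important, for which the article gives no figure. No calculation is possible.

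**The case against.** The best case against the point is that its effect may be nothing. Randomisation follows the two-week run-in and confirmed eligibility, so run-in losses fall before it and few patients may go untreated. The 15% is total dropout, not loss before the first session. Treatment is standardised, and nothing suggests that patients receive the other arm's procedure. The Trial status section describes the pilot as watching for any adverse events, which does not suggest an intention to ignore minor ones, and grading of events is commonly left to a full protocol. Most of this stands and keeps the point modest. It does not remove the express rule that puts safety under intention to treat, nor the disagreement between two sections, which a definition elsewhere would not resolve.

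A reader might infer more, and the document does not support it:

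- *That incidence is certainly understated.* This needs untreated randomised patients or an applied *important* filter; neither is established.
- *That carrying values forward hides events.* The rule does not name adverse events, and it would not change an ever/never count.
- *That unblinded staff decide which events are important.* The Assignment and blinding section says "Only the acupuncturists are allowed to know" the allocation, and events are reported at treatments among other contacts. No section says who collects or classifies them, so this is speculation.
- *That safety is definitely limited to important events.* That is true of the Outcomes wording only.

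**Conclusion.** The point holds as a modest one. Placing safety under intention to treat is a stated choice that can dilute adverse event incidence and can attribute events to a procedure the patient did not receive. The Outcomes and Statistical analysis sections also differ on whether important or all adverse events are counted.

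Incidence may be understated by 0% in relative terms if every randomised patient is needled, by 5% with three untreated patients per arm, and by at most 15% if all nine expected dropouts per arm are untreated. The illustrative 20% event rate and the numbers untreated are assumptions; only the 60 per arm and the 15% come from the article. The effect of the *important* restriction, if it applies, could be larger but cannot be sized from the document. The primary efficacy analysis is not affected.

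**What to change.** In the Statistical analysis section, limit intention to treat and last observation carried forward to efficacy. Define the safety population as all patients who received at least one session, analysed by the procedure received. Excluding adverse events from the carry-forward rule is for clarity; it will not alter an ever/never count.

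Reconcile the Outcomes and Statistical analysis sections so that both refer to all adverse events reported at treatments and follow-up interviews, with serious and treatment-related events shown as subsets.

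These are changes of wording. The small downside is recording minor events at visits that already take place; sample size and visit schedule are unchanged.
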